## Methods/design

### Study subjects

This trial will be conducted on 86 infertile men with idiopathic asthenozoospermia (the mobility of sperm < 40% and rapid progressive sperm motility < 32% [50], and with serum vitamin D levels < 30 ng / ml, who report inability to have a child after at least 1 y of marriage without using any preventive methods and with normal fertile female partner in the Infertility Clinic of Ahvaz Jahad daneshgahi, Iran. The further inclusion criteria are listed in Table 1.

**Table 1 Tab1:** Inclusion and exclusion criteria

Inclusion	
•Men aged 20 to 50 years	
•Idiopathic asthenozoospermia (the mobility of sperm < 40% and rapid progressive sperm motility < 32%	
•Serum vitamin D levels < 30 ng / ml	
•Access to the infertility clinic of Ahvaz Jahad daneshgahi, Iran	
•Inability to have a child after at least 1 y of marriage without using any preventive methods	
•Normal fertile female partner	
•No history (≤ 12 weeks) of medical therapy	
•Not having a history of epididymo-orchitis, prostatitis, genital trauma, testicular torsion, inguinal or genital surgery, urinary tract infection, or previous hormonal therapy, another genital disease (cryptorchidism, current genital inflammation or varicocele), a recent history of sexually transmitted infection, hepatobiliary disease and renal insufficiency, severe general or central nervous system disease and endocrinopathy, using cytotoxic medications, immunosuppressant, anticonvulsants, androgens, antiandrogens	
•No smoking, drug or alcohol abuse, and	
•No occupational and environmental exposure to possible reproductive toxins	
•Body mass index of < 30 kg/m^2^	
Exclusion	
• Have any acute illness	
• Use less than 90% of the prescript supplement	
• Would like to leave the study personally	
• Participate in another study	
• Immigrate	
• Not available for following-up	

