### Design

This study is a randomized, triple-blind, placebo-controlled clinical trial. There will be four study phases consisting of baseline phase I “enrolment”, baseline phase II “randomization and allocation”, treatment and follow up over 12 weeks (Fig. 1). Participants will be randomly allocated into two groups of either receiving 4000 IU/d [51, 52] vitamin D3, or a matched placebo. Participants, the researchers, and statistical counselor will be blinded in terms of the type of intervention throughout the trial. All visits will be held in the “Infertility Clinic of Ahvaz Jahad daneshgahi”, Iran during the day.

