### Sample size

The sample size was calculated based on the progressive sperm ratio as the primary variable [29]. Considering a type I error of 0.05 and 90% for the power study, 34 patients were determined for each group. Also, regarding with the attrition rate of 25%, 43 patients will be included for each group. The formula used for the sample size was as follow:
$$ n=\frac{{\left({z}_1-\frac{\alpha }{2}+{z}_1-\beta \right)}^2\left({\delta_1}^2+{\delta_2}^2\right)}{{\left({\mu}_1-{\mu}_2\right)}^2} $$

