### Statistical analysis

Intention-to-treat (ITT) and per-protocol (PP) populations will be used in the analysis. The ITT population consists of all individuals who will be randomized, whereas the PP population consists of all participants who complete the 12-week intervention. All data will be analyzed using SPSS (Version 22; SPSS Inc., Chicago, IL). Results will be expressed as mean ± SD and frequency and (percentage) for quantitative and qualitative variables respectively. The normal distribution of variables will be tested and confirmed by Kolmogorov-Smirnov test. The baseline differences of mean values between groups will be tested using independent sample t-test or Mann-Whitney U test for normal and non- normal distribution variables respectively. Analysis of covariance (ANCOVA) will be used to identify any differences between the two groups at the end of study, adjusting for baseline values and covariates (such as BMI, age, dietary intake including dietary calorie, calcium, F, selenium, vitamin C, E, A, D and zinc, physical activity, sun exposure, season, serum vitamin d, PTH and calcium). The comparison of mean values within groups pre- and post-intervention will be done by paired sample t tests and Wilcoxon signed-rank test as nonparametric alternatives for normal and non- normal distribution variables respectively. Differences will be considered statistically significant at *P* < 0.05.

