Furthermore, a higher level of prolactin along with low levels of vitamin D has been demonstrated in infertile men. The increased prolactin can inhibit spermatogenesis, damage sperm motility and reduce sperm quality through inhibition of the pulsating cycle of gonadotropin and T secretion [79, 80].

We believe that the strengths of this study are as follow: the daily dosage of vitamin D, the wide range of exclusion criteria such as smoking and having any specific disease, control of confounding factors including BW, BMI, BF%, WC, physical activity, season, dietary calorie, calcium, F, VD3, selenium, vitamin C, E, A, zinc, serum 25-OHD and PTH and considering baseline values. However, there are some limitations in this study including not selecting healthy subjects, not measuring ROS, endogenous antioxidants such as glutathione, selenium, and vitamin E and some other hormones such as inhibin. In addition, one of the possible operational issues in this study is a high probable rate of participants withdraw. For this reason a high dropout percentage (25%) will be considered in terms of calculating the sample size.

Therefore, due to the role of OS in the pathogenesis of idiopathic male infertility and also considering the antioxidant property of vitamin D and probable positive relationship between semen quality and vitamin D levels in men and since there is no clinical study on the effect of vitamin D supplementation on OS markers in men with asthenospermia and insufficient vitamin D levels or vitamin D deficiency, and also regarding with the high prevalence of vitamin D deficiency in infertile men, it seems that further clinical studies are needed in this area before any recommendation to use vitamin D supplement as part of the treatment of male infertility. Therefore, this RCT will be done to investigate the effects of the vitamin D supplementation on sperm parameters, seminal and serum levels of oxidative stress and serum endocrine factors in asthenospermia infertile men.

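### The between-group ANCOVA adjusts for an open-ended list of 17 covariates with about 64 expected completers; the Discussion describes a different set, and a short closed list would protect power and fix the model

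*Protocol article*

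**What the plan says.** The Statistical analysis section of the protocol article compares the groups at the end of study by ANCOVA, "adjusting for baseline values and covariates (such as BMI, age, dietary intake including dietary calorie, calcium, F, selenium, vitamin C, E, A, D and zinc". The same parenthesis goes on to physical activity, sun exposure, season, serum vitamin D, PTH and calcium. The words *such as* make these examples, not a closed set. One dietary item appears only as the letter F, which the abbreviation list does not expand.

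The Discussion counts covariate control among the trial's strengths: "control of confounding factors including BW, BMI, BF%, WC, physical activity, season, dietary calorie", followed by further dietary items, serum 25-OHD, PTH and baseline values.

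The Sample size section uses an unadjusted comparison of two means. "The sample size was calculated based on the progressive sperm ratio as the primary variable". "Considering a type I error of 0.05 and 90% for the power study, 34 patients were determined for each group". For attrition it adds: "regarding with the attrition rate of 25%, 43 patients will be included for each group".

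**The concern.** Covariate adjustment in a randomised trial helps when the covariates predict the outcome. Each one that does not predict it costs a residual degree of freedom and adds chance correlation with arm, which raises the standard error of the treatment effect. With some 20 adjustment terms and about 64 men that cost may not be small, and the sample size formula makes no allowance for it.

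The second issue does not depend on how prognostic the covariates are. When a list is open, several models all comply with the plan, and the one reported can be settled after results are visible. Blinding the statistical counselor to the meaning of groups A and B does not prevent this, because the p-value of an A-versus-B comparison is visible without knowing which group is active.

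**Working it through.** **1. Count the covariates.** Statistical analysis: BMI and age (2); dietary calorie, calcium, F, selenium, vitamins C, E, A, D and zinc (9); physical activity, sun exposure, season (3); serum vitamin D, PTH and calcium (3, reading the last as serum calcium). Total 17.

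Discussion: also 17. It adds body weight, body fat % and waist circumference, and omits age, sun exposure and serum calcium. The two lists name 17 + 3 = 20 distinct variables.

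**2. Degrees of freedom.** Season as a single term: 17 + 1 (baseline) = 18. Season as four levels (assumption): 16 + 3 + 1 = 20. When 25-OHD, PTH or serum calcium is itself the outcome, its baseline is already listed and one is saved.

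**3. The plan's own figures.** The 34 per group cannot be reproduced, because the article does not print the means and SDs. Solving its formula backwards gives d = (1.960 + 1.282) × √(2/34) = 0.786. The attrition step reproduces as 34 × 1.25 = 42.5, rounded up to 43 (86 in total). At 25% attrition, 86 × 0.75 = 64.5, so about 64 completers.

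**4. Power under ANCOVA.** With N men and k adjustment df, the residual df are N − 2 − k. The noncentrality is d × √[(N/4)(1 − R²)/(1 − r²)]. Here r² is the share of outcome variance explained by the adjustment terms. R² is the chance share of arm explained by them, averaged over Beta(k/2, (N − 1 − k)/2). The test is two-sided at 0.05.

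| Men analysed | Variance explained by baseline | Baseline only (k = 1) | Full list (k = 20), added terms not prognostic |
|---|---|---|---|
| 64 | 0 | 86.6% | 71.5% |
| 64 | 25% | 94.3% | 82.9% |
| 64 | 50% | 99.1% | 94.3% |
| 86 | 0 | 94.7% | 87.8% |

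At 64 men the residual df fall from 61 to 42. Mean variance inflation is (N − 3)/(N − 3 − k): 61/60 = 1.02 against 61/41 = 1.49. The standard error therefore rises by a factor of about √(1.49/1.02) = 1.21. With season as one term (k = 18) power is 73.5% instead of 71.5%.

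**5. Break-even.** At 64 men the 19 added df must jointly explain about 33% of the variance left after baseline for the full model to match the baseline-only model (33%, 33% and 35% for the three 64-man rows).

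**6. Model choice.** Null simulation with 64 men, independent covariates, an assumed baseline correlation of 0.5 and 4,000 runs. Each of three fixed models (baseline only, Statistical analysis list, Discussion list) rejects in about 5% of runs. Taking the smallest p-value of the three rejects in about 8.6%. This shows what the open wording would permit; it does not show that anyone intends it.

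**The case against.** **The 15-point loss is a worst case.** It needs every listed covariate to enter, none to be prognostic, season to have four levels and only completers to be analysed. The effect size is back-solved. If baseline explains half the variance, the full model still has 94.3% power, above the planned 90%. The Discussion also gives some rationale for age, BMI, serum 25-OHD and calcium, as possible reasons for conflicting testosterone results. All of this stands, so the loss can only be given as a conditional range. A reader might infer that the dietary items are known to predict nothing; the documents give no prognostic strength in either direction.

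**The Discussion list is not an analysis specification.** It is a sentence on strengths, introduced by *including*. A reader might infer two rival primary models, but the documents support only an inconsistency that needs aligning.

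**Details may sit in an analysis plan that is not shown.** Coding and final model form may. But the article itself names the set, leaves it open and describes it differently elsewhere, and a later plan cannot agree with both lists.

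**Missing rows.** A reader might infer that 17 covariates would empty a complete-case fit. The data sources do not support that. The nine dietary items come from one recall, and the three serum items from one blood draw. Age, BMI, activity and 25-OHD are checked before allocation, and season follows from the date. About three separate sources remain (diet recall, sun questionnaire, PTH and calcium assays). At an assumed 1 to 2% missing each, 1 − 0.99³ = 3% to 1 − 0.98³ = 6% of rows would be lost.

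**Adjustment is legitimate.** With 86 men, correcting for chance imbalance is reasonable. The objection is to a long, open list, not to adjustment.

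**Conclusion.** The point holds as a cheap improvement that should be made. The planned ANCOVA is open-ended and long for the sample: 18 to 20 adjustment df for about 64 completers. The Discussion describes a different set.

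At d of about 0.79 the cost at 64 men runs from nothing, if the added covariates explain about a third of the residual variance, to about 15 points (86.6% to 71.5%), if they explain none and baseline is also uninformative. It is about 7 points if all 86 men are analysed. The shortfall of the 86.6% itself below 90% is not a covariate effect: it comes mainly from expecting 64 completers when the calculation needs 68.

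The figures rest on the back-solved effect size, the season coding and the assumed baseline correlation, none of which the article states. The freedom to choose a model after the data needs none of these assumptions; only its illustrated size (about 8.6%) does.

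**What to change.** In the Statistical analysis section, define the primary model as arm, the baseline value of the outcome, and a short closed list of named covariates measured at visit 2 (age and season, for example), and state how season is coded. Delete *such as*. Naming the visit matters because diet, activity, sun exposure and blood are collected at both visit 2 and visit 5. Serum 25-OHD is also a primary outcome that treatment is meant to change, so a week-12 value would adjust away part of the effect.

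Move the wider diet, activity, sun and anthropometric adjustment to one labelled sensitivity analysis with a fixed list, and make the Discussion sentence match.

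The cost is wording only. The article describes the trial as still enrolling, with codes opened at the end of the study, so the change can precede unblinding. The one downside is that any dietary covariate that proves prognostic would contribute only to the sensitivity analysis.

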### Primary outcomes

The primary outcomes are as follow:
Changes in the mean serum levels of 25-OHD between and within two groups pre and post intervention in asthenospermia infertile menChanges in the mean ejaculation volume, total sperm count, percentage of motile sperm, number of sperm with normal morphology, number of live sperm in semen between and within two groups pre and post intervention in asthenospermia infertile men.

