### Baseline Phase I (Enrolment Phase): − 2 week

During visit 1, the final eligibility will be determined and a written consent will be obtained from participants by trained study staff. The information such as the procedures of the study, risks, side effects, confidentiality, voluntary participation, and right to withdraw will be provided to all participants. After consent is obtained, the study staff screens for drug abuse, obtains medical and concomitant medication histories, with eligibility determination based on the inclusion/exclusion criteria listed in Table 1. The necessary training to complete 3-day, 24-h recall questionnaires (including two week days and one weekend day) are given by a nutritionist to the participants and are asked to deliver them to the researcher during the second visit. In addition, participants are asked 2 to 7 days sexual abstinence to take semen samples. Semen and blood samples will be taken at the second visit.

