### Baseline Phase II (Allocation Phase): 2 weeks (− 1, 0 weeks)

Once a participant is determined eligible, further demographic data, dietary intake, physical activity, sun exposure, anthropometric indices will be assessed, and blood and semen samples will be obtained during visit 2.

Demographic characteristics of patients are included: age (y), marriage duration (y), infertility duration (y), education, race, physical activity, sun exposure, time of sun exposure, sun exposure area, and sun screen use. The dietary intake will be evaluated using a 3-day, 24-h recall questionnaires (including two week days and one weekend day). Total energy, macronutrient, and micronutrient intake will be estimated using nutritionist IV software. The short form of the international physical activity questionnaire (IPAQ) will be used to evaluate physical activity levels [53]. The sun exposure time will be assessed with a questionnaire [54]. Anthropometric indices will be measured after overnight fasting, with minimal clothing and without shoes. Body weight and body fat percent will be measured with light clothes, no shoes and accuracy of 0.1-kg by Omron scale (Germany). Height will be measured without shoes with the accuracy of 0.5-cm by a stadiometer. Waist and hip circumferences will be measured by measuring meters (Seca, Germany). BMI will be computed by dividing the weight (kg) by the height squared (m^2^).

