### Semen and blood samples

Semen samples will be obtained after 3 days of sexual abstinence. All semen samples will be held at 37C until the liquefaction. The sperm quality parameters such as ejaculate volume, total sperm count, sperm concentration, motility grade and sperm with normal morphology (%) will be assessed according to the WHO criteria [55]. The other biochemical analysis such as seminal levels of oxidative stress markers including malondialdehyde (MDA), 8-hydroxy-2- Dioxy Guanosine (8-OHDG) and total antioxidant capacity (TAC) and calcium will also be analyzed. Sperm DNA fragmentation will be assessed using sperm chromatin dispersion (SCD) method [11, 12].

Moreover, 10 cc of intravenous blood samples will be collected from patients to analyze biochemical parameters including 25 hydroxyvitamin D (25-OHD), oxidative stress index (TAC and MDA) and 8-OHDG, Sex hormones (total testosterone, estradiol (E2), luteinizing hormone (LH), follicle-stimulating hormone (FSH), sex hormone-binding globulin (SHBG), prolactin), parathyroid hormone (PTH), osteocalcin, calcium, and phosphorus.

The measurement of serum calcium and phosphorus and seminal calcium will be done using calorimetric method. Seminal and serum levels of vitamin D, TAC, MDA, 8-OHDG, PTH, osteocalcin, Testosterone, E2, SHBG, luteinizing hormone (LH), follicle-stimulating hormone (FSH), and prolactin will be assessed by enzyme-linked immunosorbent assay (ELISA).

During Baseline Phase II, the participants will be excluded if they have:
Body mass index (BMI) > 30 kg/m^2^Normal semen samples analysis for sperm motility (the mobility of sperm > 40% and rapid progressive sperm motility> 32%)Sufficient serum levels of 25OHD levels (> 30 ng / ml)Intense physical activity (> 3000 met/cal/week)

In visit 3 patients will be randomly allocated to either group A, receiving 4000 IU/d [51, 52] vitamin D3, or group B, receiving a matched placebo for 12 weeks (Randomization and blinding method described above).

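### Within-arm pre/post tests share primary status with the between-group ANCOVA, although low motility and low 25-OHD at the baseline sample are entry conditions, so both are expected to rise untreated

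*Protocol article*

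**What the plan says.** Under Primary outcomes, the first item is "Changes in the mean serum levels of 25-OHD between and within two groups pre and post intervention". The second lists five semen measures and closes with "number of live sperm in semen between and within two groups pre and post intervention in asthenospermia infertile men". The Secondary outcomes are framed in the same way.

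Under Statistical analysis, two kinds of test stand side by side. For the treatment comparison, "Analysis of covariance (ANCOVA) will be used to identify any differences between the two groups at the end of study, adjusting for baseline values". For change inside each arm, "The comparison of mean values within groups pre- and post-intervention will be done by paired sample t tests and Wilcoxon signed-rank test". One significance rule, P < 0.05, covers both. The section does not rank the ANCOVA above the paired tests and does not call the paired tests descriptive.

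On timing, the Baseline Phase I section says "Semen and blood samples will be taken at the second visit", and the Baseline Phase II section repeats that "blood and semen samples will be obtained during visit 2". The Semen and blood samples section then says "During Baseline Phase II, the participants will be excluded if they have", among other things, "Normal semen samples analysis for sperm motility (the mobility of sperm > 40% and rapid progressive sperm motility> 32" percent, or 25-OHD above 30 ng/ml. Randomization follows at visit 3. The next samples described are those of visit 5, 12 weeks after baseline.

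**The concern.** When men are kept because a variable measurement came out low, some of them were low by chance that day, and their next value is higher on average. This is regression to the mean. It happens on placebo as well as on vitamin D, and a paired test in one arm cannot separate it from benefit. Motility and 25-OHD are both primary variables and both selection variables, and the visit 2 value serves for selection and as baseline.

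The paired tests also make no adjustment for season, which can move 25-OHD over 12 weeks. The ANCOVA lists season and sun exposure as covariates.

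What is at stake is interpretation. As the outcomes are defined, a significant rise in the vitamin D arm meets the description of a primary result even if the two arms do not differ. The Practical aims section ties a recommendation for supplementation to benefit being confirmed in this study, and no sentence says that a within-arm P value cannot serve as that confirmation.

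**Working it through.** **Number of primary tests.** Primary variables: 25-OHD, ejaculate volume, total count, percent motile, normal morphology, live sperm = 6. Each has one between-group test and one paired test per arm: 6 × (1 + 2) = 18, three times the 6 between-group tests.

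**Is selection made on the baseline sample?** Samples are taken at visit 2, men above the limits are excluded in that phase, and randomization is at visit 3. No further sample is described between exclusion and treatment. So the answer is yes.

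**Size of the effect.** The plan gives no figure to reproduce here: it states no clinic mean, SD or test-retest correlation for motility or 25-OHD. These are assumptions.

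Inputs from the protocol: cut-off 40% for motility; 34 per group before attrition and 43 enrolled per group (Sample size section); 25% attrition, so 43 × 0.75 = 32.25, about 32 completers.

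For normal measurements with mean μ, SD σ and between-sample correlation ρ, selected below a cut, let c = (cut − μ)/σ. The expected rise with no treatment effect is

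(1 − ρ) × σ × φ(c)/Φ(c).

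Base case, assuming μ = 40, σ = 15, ρ = 0.7:
- c = 0 and φ(0)/Φ(0) = 0.399/0.5 = 0.798.
- Rise = 0.3 × 15 × 0.798 = 3.6 percentage points.
- Baseline variance after selection = 225 × (1 − 0.798²) = 81.8.
- Variance of the change = 0.3² × 81.8 + 225 × (1 − 0.7²) = 7.4 + 114.8 = 122.1, so SD = 11.05.
- At n = 34 the standard error is 11.05/√34 = 1.90, and 3.6/1.90 = 1.89 against a critical t of about 2.03. The paired test is significantly positive in about 45% of trials. At n = 32 it is about 43%.

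Simulation of arms with no treatment effect agrees: a rise of 3.6 points and 42% to 45% significant. The nominal rate in that direction is 2.5%.

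| Selection assumed (n = 32–34) | Base case | Mean 35–45, SD 12–15, ρ 0.5–0.8 |
|---|---|---|
| Visit 2 value below 40 | 42–45% | about 16% to 93% |
| Visit 2 value and an earlier record value both below 40 | 22–24%, rise 2.4 points | about 10% to 70% |

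The simulation uses the 40% motility limit alone and leaves out the rapid-progressive limit.

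**A wider check in SD units**, usable for any selection variable including 25-OHD, varies the share of screened men below the cut:

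| Share below cut | ρ | Expected rise (SD) | Significant rise, n = 34 | n = 43 |
|---|---|---|---|---|
| 20% | 0.5 | 0.70 | 99% | about 100% |
| 40% | 0.7 | 0.29 | 61% | 73% |
| 60% | 0.7 | 0.19 | 31% | 40% |
| 80% | 0.9 | 0.035 | 7% | 7% |

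In the same simulations the baseline-adjusted ANCOVA between arms rejected in 4.9% (n = 34) and 4.6% (n = 43) of trials, as it should.

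**The case against.** The strongest reply is that the valid analysis is already in the plan. The trial is randomized and placebo-controlled, regression to the mean acts equally on both arms, and the ANCOVA keeps its error rate. This stands. A reader might infer that the efficacy comparison is biased, or that the sponsor intends to claim efficacy from a within-arm P value. The protocol supports neither. What it does is leave that route open, by defining the outcomes so and not subordinating the paired tests.

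A second reply is that the Recruitment process section has records reviewed before men are contacted, so visit 2 may be a second low reading. The section does not list the criteria checked. If an earlier motility value was among them, the base-case figure falls by about half, to 22–24%, still far above 2.5%.

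A third is that the size is assumed. That stands too. If nearly all screened men are well below the limits, or repeat measurements are very stable, the effect is small, as the last row of the second table shows.

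A fourth concerns reach. A reader might infer that all six primary variables will rise. Only motility and 25-OHD are selected on directly. Volume, count, morphology and live sperm are affected only as far as their variation is correlated with these.

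Finally, a fuller analysis plan might rank the tests. That would help, but the point rests on what the outcome definitions state, not on something left out.

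**Conclusion.** The point holds as a defect of outcome definition and interpretation, not of the between-group analysis. Followed as written, the plan can yield a significant primary result in the vitamin D arm with no treatment effect, and 12 of its 18 primary tests are within-arm tests that cannot show one. The direction for motility and 25-OHD follows from the design, given that repeat values vary within a man. The size does not: for motility, roughly 16% to 93% of arms without a treatment effect would show a significant rise under the assumed means, SDs and correlations, or roughly 10% to 70% with pre-screening on an earlier low value. These ranges illustrate the risk and are not estimates for this clinic. The change should be made, and because a valid analysis is already planned, it does not call the design into question.

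**What to change.** - In Primary outcomes and Secondary outcomes, strike the within-group part, so that each outcome is the between-group difference at 12 weeks adjusted for baseline.
- In Statistical analysis, say that within-arm changes are reported descriptively (mean and SD) and carry no efficacy inference. Take the paired t and Wilcoxon tests out of the inferential plan.
- State that every efficacy conclusion rests on the baseline-adjusted between-group difference with its 95% CI.

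The cost is wording only: no extra men, visits or assays, and fewer tests. The sponsor gives up within-arm P values as evidence of efficacy. The Trial time-scale section places the trial in enrolment in 2021, and the codes are to be opened only at the end, so the change can be made and dated before unblinding if that has not yet happened.
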